## Abstract

**Background:**

The Healthy School Recognized Campus initiative bundles multiple school- and research-based programs for children and adults to improve physical activity and nutrition outcomes that affect cardiovascular disease risk. This study aims to test the individual and combined impact of three implementation strategies on implementation and effectiveness outcomes.

**Methods:**

Using the Multiphase Optimization STrategy (MOST) framework and a cluster randomized full factorial study design, two cohorts (*n* = 8; *n* = 16 total) of public elementary schools in North and East Texas will be randomized to receive combinations of the three implementation strategies – additional resources, school-to-school mentoring, and enhanced engagement – over one academic year. We will survey program implementers (e.g., Extension agents, school staff, administrators) to determine the dose of the Healthy School Recognized Campus initiative that each student receives. We will objectively measure changes in students’ MetS risk, cardiovascular fitness measured via the Progressive Aerobic Cardiovascular Endurance Run, dermal carotenoids (an estimate of fruit and vegetable intake) measured via the Veggie Meter, and body mass index pre- and post-intervention. The individual and combined (e.g., synergistic, antagonistic) impact of strategies will be evaluated after each cohort using a general linear model framework, and strategies will be modified and prepared for testing in a future randomized controlled trial.

**Discussion:**

By using rigorous implementation science frameworks, developing three implementation strategies, and evaluating implementation and effectiveness outcomes, this study aims to determine which implementation strategy or combination of strategies have the biggest impact on the Healthy School Recognized Campus initiative.

**Trial registration:**

Registered at clinicaltrials.gov on August 2nd, 2023 (NCT05977959).

## Introduction

1

In the United States, approximately one in three youth are overweight, and 85% of overweight youth have at least one metabolic syndrome (MetS) risk factor that increases their chance of developing chronic diseases (e.g., cardiovascular disease, diabetes) (1, 2). In 2000, the prevalence of MetS in the United States was about 6.4%; however, the prevalence rate among obese children has been found to be as high as 50% (3). Given that the rate of body mass index (BMI) acceleration doubled during the COVID-19 pandemic, the prevalence of MetS in youth is also likely to increase in the coming years (4).

Established by the U. S. Department of Health and Human Services, The Community Preventive Services Task Force has identified the delivery of school based physical activity and nutrition evidence-based programs (EBPs) as an effective approach for improving obesity, and consequently, MetS and other chronic disease risk factors among youth (5–8). Schools are also a critical setting to improve health behaviors (i.e., physical activity and nutrition), as almost 57 million U. S. children and adolescents attend school, spending an average of 6.5 h there each day (9). Experts recommend that schools help students achieve 30 min of daily physical activity, eat ≥2 vegetables, and a fresh fruit each day, but these goals are rarely met (10, 11). Accordingly, the delivery of more EBPs that promote physical activity and fruit and vegetable consumption are essential for changing youths’ MetS risk.

One way to improve the number of EBPs delivered is the use of bundling approaches or care bundles, whereby a set of evidence-based practices or programs are implemented at the same time in coordination with one another (12, 13). Theoretically, the use of bundled approaches should improve behavioral or health outcomes better than a single program alone; however, most bundled approaches have been tested in health care settings, and results from these studies show mixed or inconclusive findings (13). In the school setting, previous research has demonstrated that for each additional physical activity or nutrition program that a school implemented, the odds were 4% higher for students meeting recommended standards for BMI (14). The use of bundled approaches is also highly relevant for school settings, as most schools are already delivering multiple physical activity (e.g., recess, physical education, after school programs) and/or nutrition programs (e.g., health education, cooking classes) concurrently, and bundled approaches align with conceptual frameworks for improving multiple aspects of student health (e.g., Whole School, Whole Community, Whole Child framework) (15–18).

Still, schools face critical challenges for concurrently delivering multiple EBPs. For example, one systematic review identified 22 different barriers that affect schools’ willingness to implement EBPs (e.g., time, availability/quality of resources, school climate) (19). Further, barriers/facilitators to program implementation are often specific to a staff member’s role within the project (e.g., teachers report resources as a barrier, whereas principals report staff turnover) (20, 21), the school’s context, or the EBPs being delivered, which necessitates the development of optimized implementation strategies (i.e., methods tailored to specific implementation barriers) (22, 23). Optimization is the process of balancing intervention effectiveness with its ability to be implemented (e.g., affordability, scalability, efficiency) (24, 25). Accordingly, implementation strategies that are optimized to support the delivery of bundled EBPs in schools can improve the number and quality of EBPs implemented, and ultimately, health outcomes (26). For example, one study found that when school staff perceived successful implementation of physical activity and nutrition programs, students were 32% more likely to meet recommended standards for cardiovascular fitness (14).

Accordingly, we aim to improve the implementation and effectiveness of the Healthy School Recognized Campus (HSRC) initiative, which promotes the delivery of physical activity and healthy eating programs by bundling AgriLife Extension’s school- and research-based programs. For a school to be recognized as a HSRC, they are required to host a school-wide walking challenge to increase students’ physical activity (i.e., Walk Across Texas), at least one other AgriLife Extension program for students, and at least one AgriLife Extension program for adults. The aims of this study are to describe the protocol for a cluster randomized factorial trial to: (1) evaluate the individual and combined (synergistic or antagonistic) impact of three implementation strategies on the delivery of bundled physical activity and nutrition programs and (2) evaluate the effectiveness of a bundled approach on improving MetS among elementary school-aged children.

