### Study setting

2.1

We will recruit two cohorts of eight schools from the North and East regions of Texas to participate in this study. Texas A&M AgriLife Extension defines North and East Texas as a 44-county service area. From west to east, this region includes Cooke, Denton, and Tarrant counties – which includes the Dallas-Fort Worth metroplex – and all other Texas counties east of the Trinity River. From north to south this region includes counties along the Oklahoma border, and extends south to Jasper/Newton counties (a full list of counties can be found at agrilifeextension.tamu.edu/about-2/district-offices-regional-centers/).

Counties in the North and East Texas AgriLife regions have some of the highest rates of cardiovascular disease in the country; and the prevalence of MetS is around 9%. The average rate of cardiovascular disease in these 44 counties is 556.3 deaths per 100,000 people over 18 years of age, which is substantially higher than the average of all Texas counties (442.5 per 100,000 people) and the average of all counties in the United States (432.3 per 100,000 people) (27). The rates in these counties are also higher for deaths from heart disease (430.6 vs. 334.5 in Texas vs. 325.7 in the United States), deaths from stroke (92.14 vs. 80.1 in Texas vs. 75.7 in the United States), and preventable/avoidable deaths from cardiovascular diseases (403.4 vs. 324.6 in Texas vs. 310.3 in the United States) (27). Similarly, these counties also have a higher average prevalence of cardiovascular disease risk factors than the average of other Texas counties, including for high blood pressure (39.1% vs. 37.4% in Texas), high cholesterol (40.0% vs. 39.6% in Texas), diabetes (8.2% vs. 7.9% in Texas), obesity (23.1% vs. 21.4%) leisure time physical inactivity (17.7% vs. 16.1%) and smoking (18.3% vs. 17.0%) (27).

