### Study eligibility

2.3

For a school to be eligible to participate, it must be a public elementary school located in North or East Texas implementing the HSRC initiative (28, 29). For implementers to be eligible to participate, they must be 18 years old or older, be able to read and communicate in English, and be affiliated with a school that is eligible to participate.

For students to be eligible to participate in the study, they must be enrolled in the 5th or 6th grade, be at least 10 years old, have no known motor or cognitive impairments or other health conditions that would prevent them from completing assessments. The age of 10-years-old was selected because diagnostic criteria for MetS do not exist for children under that age (3). Students who have reported ever losing consciousness from pain or at the sight of blood will also be excluded to assist in diminishing the risk of fainting during assessments. Students must also be able to speak, read and write in English. For parents to be eligible to participate, they must be 18 years old or older with children enrolled in the participating schools and grade levels.

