#### Healthy school recognized campus (HSRC) initiative

2.4.2

For this study, all schools will agree to participate in the HSRC initiative. The HSRC initiative promotes the delivery of physical activity and healthy eating programs by bundling AgriLife Extension’s school- and research-based programs. For a school to be recognized as a HSRC, they are required to host a school-wide walking challenge to increase students’ physical activity (i.e., Walk Across Texas), at least one other AgriLife Extension program for students, and at least one AgriLife Extension program for adults (examples in Table 1; full list of programs found at https://texas4h-hsrc.com/). Including both interventions for students and their caretakers (i.e., teachers or parents) is also a benefit of this bundled approach, as interventions that address more than one level of the ecological model (e.g., intrapersonal, interpersonal, organizational) can be more effective than single level interventions (30–32). Programs are delivered by one or more Extension agents (i.e., health educators) in the county where the school is located (33, 34), and once the initiative’s requirements are complete, schools receive recognition via a banner and/or at a local school meeting (e.g., school board, school health advisory council).

**Table 1 tab1:** Examples of healthy school recognized campus’ research-based programs.

Program	Description	Research
Youth		
Walk Across Texas! (Youth) (69, 70)	8-week program designed to help youth across Texas establish the habit of regular physical activity using a fun and motivating team approach.	- Doubled the number of steps taken over the course of the program. - Increased the amount of time that students were active with their parents. - Decreased BMI percentile.
Learn Grow Eat and Go! (70, 71)	10-week program that teaches students about gardening, healthy eating, and being active.	- Increased the number of vegetables tasted, vegetable preferences, and nutrition knowledge. - Decreased BMI percentile.
Choose Health: Food, Fun and Fitness (72–74)	6-session program that encourages healthy eating and fitness through hands-on activities and experiential education.	- Improved overall dietary intake, vegetable intake, fruit intake. - Reduced soda/fast food intake. - Read nutrition labels and share about healthy eating with families more often. - More likely to try new food. -Increased frequency of doing physical activities.

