#### Randomization

2.4.6

In each of the two cohorts, schools will be randomized to one of eight experimental conditions and will receive a different combination of implementation strategies (Table 2). In each school year, four schools will receive each implementation strategy, and four schools will not (all schools will receive the website as a constant implementation strategy). Schools and data collectors will be blinded to randomized conditions until a school completes data collection. An interim analysis (following processes outlined below) will be conducted between the two cohorts to determine if implementation strategies should be removed and/or replaced, as well as if any of the current implementation strategies should be modified.

**Table 2 tab2:** Randomized experimental conditions for this study.

Experimental condition	Constant	Factor 1	Factor 2	Factor 3
1	Website/TEKS alignment	None	None	None
2	Website/TEKS alignment	None	None	Enhanced engagement opportunities
3	Website/TEKS alignment	None	School-to-school mentoring	None
4	Website/TEKS alignment	None	School-to-school mentoring	Enhanced engagement opportunities
5	Website/TEKS alignment	Additional resources	None	None
6	Website/TEKS alignment	Additional resources	None	Enhanced engagement opportunities
7	Website/TEKS alignment	Additional resources	School-to-school mentoring	None
8	Website/TEKS alignment	Additional resources	School-to-school mentoring	Enhanced engagement opportunities

Each of the 8 conditions will be randomized one time per cohort.

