#### Statistical and power analysis

2.6.1

This is an optimization study to screen and refine components of a support strategy for the HSRC initiative in preparation for a fully powered randomized controlled trial; thus, this study is not fully powered to examine differences in implementation or effectiveness outcomes (60). To analyze outcomes, we will use univariate and bivariate statistics to determine the distribution of outcome measures and to identify relevant covariates (61). To test between-implementation strategy differences on implementation and effectiveness outcomes, students at schools with and without each implementation strategy (independent variable) will be evaluated using a generalized linear model framework. Baseline scores will be added as a covariate (when applicable), post-intervention score is the outcome, and school is a clustering variable (62). Other covariates (e.g., school size), identified in the preliminary bivariate analyses, will also be included in the model. If missing data occurs, we will mitigate potential biases by analyzing multiple imputed datasets under an intention-to-treat approach (63). Analyses will be compared to per-protocol analyses (64). Interaction effects between strategies are normally small in behavioral trials; however, we will review plots of combinations of strategies to determine if a specific combination of strategies warrants further evaluation. If so, we will add an interaction term to our model. We will calculate standardized effect estimates for each strategy (i.e., Cohen’s *d*), compare effect estimates to make decisions about which components to include in the final support strategy, and report these estimates in our results.

As the goal of this project is to refine and optimize implementation strategies for testing in a future trial, we will conduct an interim analysis following the first cohort of schools using the approach outlined above. This analysis will be repeated following the second cohort of schools. Depending on the results of the interim analysis and potential changes to the strategies that result from the interim analysis, we will conduct a pooled analysis across both cohorts, unless the implementation strategies undergo substantive modifications between cohorts, in which case we will only report the individual results from each cohort.

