Finally, the HSRC initiative bundles programs within the school setting to try to improve physical activity, healthy eating, and MetS risk among students. More specifically, all students at the school participate in an 8-week school-wide walking program (i.e., Walk Across Texas) (69, 70), and smaller groups of students at the school (e.g., physical education class, after-school club) participate in additional programming. This type of bundled approach is ideal for Extension agents, as once they start delivering programs at the school, it is often easier to implement additional programs within the school setting. Additionally, schools are an important setting to improve physical activity and diet quality among youth, as students spend an average of 6.5 h there each day for over 180 days each year (9), and school-based programs are an evidence-based approach for improving obesity outcomes (5–8). Still, given that bundled approaches have had mixed effectiveness in the clinical setting (13), it is unclear if this type of bundled approach has positive effects on students’ behavioral (i.e., physical activity and healthy eating) and health outcomes within the school setting. Thus, our study will evaluate changes in health outcomes over the course of one school year. Furthermore, as the HSRC initiative also requires that parents and/or school staff participate in a physical activity and healthy eating program – recommendations aligned with school health and ecological models (15–18)– we will evaluate physical activity and nutrition outcomes in these groups to determine if HSRC has any impact beyond students. These results can help to inform further modification to the way the HSRC initiative is designed and implemented within the school setting.

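### Aim 2 claims the effect of the HSRC bundle on metabolic syndrome, but every school delivers HSRC, so the design identifies only the effects of the three add-on strategies

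*Protocol article*

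**What the plan says.** Section 1 (Introduction) lists two aims. The first concerns the three implementation strategies. The second is to "evaluate the effectiveness of a bundled approach on improving MetS among elementary school-aged children". Section 3.1 (Conclusion) repeats both.

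On exposure, Section 2.3 requires of a school that "it must be a public elementary school located in North or East Texas implementing the HSRC initiative". Section 2.4.2 adds: "For this study, all schools will agree to participate in the HSRC initiative". 

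On randomization, Section 2.4.6 says that "schools will be randomized to one of eight experimental conditions and will receive a different combination of implementation strategies". Its Table 2 shows that condition 1, with none of the three strategies, still has the website. By Section 2.4.2 it has HSRC as well.

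On analysis, Section 2.6.1 says that "students at schools with and without each implementation strategy (independent variable) will be evaluated using a generalized linear model framework", with the baseline score as covariate, the post-intervention score as outcome and school as cluster.

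The Discussion (Section 3) remarks that it is not known whether such a bundle benefits students in schools, and continues: "Thus, our study will evaluate changes in health outcomes over the course of one school year". Sections 2.5.2 and 2.5.5 give as the reason for the implementer and parent behavior measures finding out whether HSRC programming affected those groups.

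**The concern.** The effectiveness of a bundle is a contrast between having it and not having it. This trial has no group without it: no untreated, waitlist, external or historical comparator is described. The stated model answers a different question, namely what a strategy adds where HSRC is already being delivered.

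The two questions can have different answers. If HSRC works well and every school delivers it adequately without extra support, the strategy contrasts will be near zero. They neither estimate nor bound the effect of the bundle.

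What remains for aim 2 as worded is change from baseline to follow-up, and the Discussion points the reader there. At stake is whether a shift in metabolic syndrome, fitness, carotenoids or BMI over a school year could be put forward as a result of HSRC, for students and likewise for parents and implementers.

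**Working it through.** **Inputs from the article**
- Schools: "We will recruit two cohorts of eight schools from the North and East regions of Texas to participate in this study" (Section 2.1), so 2 × 8 = 16.
- Students: about 20 per school (Section 2.4.5). 20 × 16 = 320, which reproduces the stated total.
- Allocation: "In each school year, four schools will receive each implementation strategy, and four schools will not" (Section 2.4.6). That is 4 against 4 per cohort, and 8 against 8 if the cohorts are pooled.
- Schools without HSRC: 0 of 16 (Sections 2.3 and 2.4.2).

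**Step 1. The between-school model.** Write the school mean as μ + βH·HSRC + β1·F1 + β2·F2 + β3·F3. HSRC equals 1 in all 16 schools, so its column is identical to the intercept. The 16 × 5 design matrix has rank 4. Only the sum μ + βH can be estimated, and βH cannot. β1, β2 and β3 remain estimable.

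**Step 2. The within-school change.** Let τ be the change that would have occurred anyway. Then mean change = τ + βH·HSRC = τ + βH in every school. The columns intercept, time and time × HSRC have rank 2 of 3. Again only the sum is identified. More schools or students would estimate that sum more precisely without separating its parts.

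**Step 3. What can sit in τ.** Baseline runs from 1 August to 31 October and follow-up from 1 April to 31 May (Section 2.5). The interval is therefore between 152 days (31 October to 1 April) and 303 days (1 August to 31 May), plus one day if the school year contains 29 February.
- Season differs by construction.
- The shuttle run is done twice, so familiarity can change the lap count.
- Growth is partly handled. BMI is a percentile on growth charts (Section 2.5.3.4), the waist criterion is specific to age and sex (2.5.3.1), and the fitness equation includes age, height, weight and sex (2.5.3.2).
- The other four metabolic syndrome criteria (triglycerides, HDL-C, blood pressure, glucose) use fixed cut-offs, so maturation in those is not normed out.

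**Step 4. Illustration only.** The article plans no pre-post test, so the following is an assumption throughout: a two-sided 0.05 test of mean change in a continuous outcome, no HSRC effect, and background drift d in SDs of the change score.

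SE = √[(1 + 19·ICC)/320]. Rejection probability = Φ(d/SE − 1.96) + Φ(−d/SE − 1.96).

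Example: ICC 0.01 gives SE = √(1.19/320) = 0.061. With d = 0.1, d/SE = 1.64 and the probability is 0.375.

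| ICC of change (assumed) | d = 0.1 | d = 0.2 | d = 0.3 |
|---|---|---|---|
| 0.01 | 0.375 | 0.907 | 0.998 |
| 0.05 | 0.249 | 0.726 | 0.970 |
| 0.10 | 0.183 | 0.556 | 0.883 |

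With d = 0 the rate is the nominal 0.05. These are normal approximations; with only 16 clusters a t reference would lower them somewhat. They do not describe binary metabolic syndrome.

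**The case against.** The best reply is that the article already states the right question elsewhere. The Abstract (Background), Section 2.2 and Section 2.6.1 all frame the study as testing how the strategies affect implementation and effectiveness outcomes. The decision that the trial serves, which components to carry forward, rests on those randomized contrasts. This stands, and it limits the matter to the wording of an aim and its interpretation.

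Three stronger readings are tempting, and the article does not support them.
- A reader might infer that the sponsor will test pre-post change and report it as program effect. Section 2.6.1 specifies no such test. The Discussion says only that changes will be evaluated, though the sentence before it raises the bundle's own effect. That justifies a warning, not a prediction.
- A reader might infer that nothing can be learned about exposure. Section 2.5.1 calculates a dose for each student, and the Discussion says that only smaller groups receive programs beyond the walking challenge. A dose-outcome analysis is possible. It would not be randomized, and it has no planned zero-dose group because all students take part in the walking challenge. That a condensed article sets out no dose model is not a fault.
- A reader might take the rates in the table as the trial's error rate. The drift and ICC are assumed, so the table shows a mechanism and not a size.

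That the study is declared not fully powered does not answer the point, since that concerns precision. A separate analysis plan could add models but could not supply schools without HSRC.

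**Conclusion.** The point holds in a limited form. As worded in Sections 1 and 3.1, aim 2 promises a causal effect of the bundle that the design cannot identify. With 0 of 16 schools unexposed, that effect is fully aliased with the intercept and, over time, with background change. This conclusion needs no numerical assumption. The claim that uncontrolled change might mislead depends on a drift that the article does not quantify. Norming for age and sex absorbs part of the growth component, but not season or test familiarity.

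This should be corrected, but it is not a failure of the trial. The strategy effects on student outcomes remain validly randomized, and the selection of components does not depend on aim 2 as worded.

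**What to change.** 1. In Sections 1 and 3.1, restate aim 2 as evaluating the effect of the three implementation strategies on student metabolic syndrome, fitness, carotenoids and BMI. This matches the Abstract and Sections 2.2 and 2.6.1.
2. In Section 3, say that change between baseline and follow-up is descriptive and does not measure the effectiveness of HSRC. Make the same statement for implementers in Section 2.5.2 and for parents in Section 2.5.5.
3. If an exposure-outcome analysis is done with the student-level dose from Section 2.5.1, label it observational.

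The change is to wording only. Randomization, data collection and the stated model stay as they are. The downside is a less ambitious claim: the trial would no longer promise to say whether the bundle itself improves metabolic syndrome.
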